# Acupoint catgut embedding for chronic non-specific low back pain: A protocol of randomized controlled trial

**DOI:** 10.3389/fnins.2023.1106051

**Published:** 2023-02-01

**Keywords:** chronic non-specific low back pain, acupoint catgut embedding, traditional Chinese medicine, randomized controlled trial, protocol, acupuncture

## Abstract

**Clinical trial registration:**

https://www.chictr.org.cn, identifier ChiCTR2200059245.

## 1. Introduction

Low back pain, a global high incidence and high burden disease, can greatly affect the quality of life of patients, and cause motor dysfunction or even disability (Knezevic et al., 2021). A systematic review of thirteen studies from Northern Europe, North America, and Israel reported that the prevalence of lower back pain ranged from 1.4 to 20.0%, with an annual incidence of 0.024 to 7%, and was highest in the United States (Fatoye et al., 2019). The incidence of chronic low back pain is expected to increase as the population ages, and as technological advances lead to increasingly sedentary lifestyles (Knezevic et al., 2021). A systematic analysis of the global burden of disease showed that low back pain increased the number of years lived with disability by 17.8% between 2007 and 2017 (Disease et al., 2018). A study comprehensively estimated the cost of care for non-severe low back pain episodes in hospitals in three Australian cities over a 5-year period, and showed that the average direct hospital cost for low back pain episodes was AUD$2959 (Coombs et al., 2021). It is estimated that more than $100 billion was spent annually on treating patients with low back pain in the United States (Katz, 2006). Most low back pain is non-specific (commonly cited as 90%) (Knezevic et al., 2021). Currently, for the management of patients with non-specific low back pain, pharmacological (non-steroidal anti-inflammatory drugs, weak opioids, and muscle relaxants) and non-pharmacological (exercise therapy, spinal manipulation, psychotherapy, and physiotherapy) treatments are recommended by guidelines (Vitoula et al., 2018). However, the treatment of patients with chronic non-specific low back pain (CNLBP) remains a great challenge. For example, oral non-steroidal anti-inflammatory drugs (NSAIDs) are recommended to be used with caution and not continuously, considering gastrointestinal and cardiovascular adverse events (Davis and Robson, 2016). Therefore, it is necessary to explore effective and safe non-pharmacological therapies.

Acupuncture, an important part of traditional Chinese medicine (TCM), has been proven to play a critical role in pain management and function recovery, especially for the treatment of CNLBP (Huang et al., 2021). Acupoint catgut embedding (ACE) is an innovative acupuncture method combined with traditional theory and modern materials, which embeds absorbed catgut into the acupoints, where the catgut will undergo softening, liquefaction, and absorption, thereby stimulating the acupoints for a long time (Teng et al., 2022). Compared with traditional acupuncture, ACE not only has the advantages of easy operation, strong stimulation, and long-lasting therapeutic effect, but also extends treatment interval patterns and reduces the discomfort caused by frequent acupuncture treatments, which can make up for the deficiencies in traditional acupuncture and improve patient compliance (Zhang et al., 2012). Previous preclinical studies have elucidated the mechanism of ACE in the treatment of pain. For example, in an *in vivo* experiment, ACE was shown to have a long-lasting analgesic effect on complete Freund’s adjuvant-induced inflammatory pain in rats, which was associated with activation of spinal 5-HT1AR, inhibition of GluN1 phosphorylation, and thus inhibition of Ca^2+^-dependent signaling (Cui et al., 2019). Another study suggested that ACE may exhibit antinociceptive effects by inhibiting Sig-1R regulation of p38 MAPK (Du et al., 2017). In recent years, a growing body of clinical evidence supports the use of ACE for the management of painful conditions. For example, a meta-analysis showed that ACE is beneficial for the relief of neck pain (Jo et al., 2022). However, to our knowledge, no clinical study on ACE for the treatment of CNLBP has been reported. Based on the current conditions, we will conduct a well-designed RCT to discuss the efficacy and safety of ACE, by comparing with a sham control in the treatment of CNLBP.

## 2. Methods

### 2.1. Design and setting

The present study will be a prospective, randomized, patient-assessor-blinded, sham-controlled trial. A total of 82 participants will be recruited for the trial in Guangzhou Panyu Hospital of Chinese Medicine. Participants will be divided randomly at a ratio of 1:1 into the ACE group or the sham ACE group. The trial will contain an enrolment and allocation period of 3 days, an 8-week intervention period, and a 6-month follow-up period. The flow chart of the study procedure is shown in Figure 1. This study will be conducted in accordance with the Declaration of Helsinki, the Consolidated Standards of Reporting Trials (CONSORT) (Schulz et al., 2010) and the Standards for Reporting Interventions in Controlled Trials of Acupuncture (STRICTA) guidelines (MacPherson et al., 2010) in trial design and reporting. Any modifications to the protocol that may affect the conduct of the study will be expected to draft a formal modification of the protocol. Such update will be determined by the project management group and approved by the ethics committee, before the modification being placed into practice. This trial has been registered at the Chinese Clinical Trial Registry, numbered ChiCTR2200059245.

**FIGURE 1 F1:**
[figure not shown]
Flow chart of the study procedure.

### 2.2. Recruitment

The recruitment advertisement for eligible participants will be placed on WeChat, official website of the hospital, and the waiting hall of the outpatient clinic, from April 2022 to December 2024. Eligible individuals who agree to participate in the study will sign written informed consents. By the way, participants will be notified that they are at liberty to withdraw from the study without any negative effects on their future treatments. After recruitment, the characteristic of participants will be preserved by dedicated personnel, which cannot be disclosed or used by unauthorized individuals at any time or for any reason.

### 2.3. Participants

#### 2.3.1. Diagnostic criteria

The diagnostic criteria for non-specific lower back pain are as follows: (1) pain or discomfort is located in the lumbar region with or without related radiation symptoms to lower extremities; (2) the history of low back pain lasts for more than 12 weeks; (3) the straight leg raising test is negative; and (4) there are no lumbar spine specific diseases diagnosed with imaging examination (e.g., presence of radiculopathy, osteoporosis, cord compression, or cancers). All potential participants will be first screened by a specialist with 20 years of clinical experience based on the diagnosis criteria.

#### 2.3.2. Inclusion criteria

Participants must meet with the following inclusion criteria: (1) 18–60 years old; (2) suffer from ongoing low back pain; (3) the visual analog scale (VAS) of low back pain intensity assessment is greater than 4 cm, but lower than 7 cm; and (4) participate voluntarily in this study, signing written informed consent. The inclusion process will be conducted by a specific researcher, after being assessed by diagnosis criteria.

#### 2.3.3. Exclusion criteria

Participants who meet any of the following conditions will be excluded: (1) cauda equina syndrome with bladder, bowel, or sexual dysfunction; (2) tumors, fractures, infections in the spine, or skin diseases in the lumbar region, or hemostatic disorder; (3) other serious diseases, such as cardiovascular, kidney, or liver diseases; (4) with diabetes or other diseases characterized by skin and subcutaneous tissue dysfunctions in absorption and renovation; (5) cognitive impairment or serious mental illnesses, such as schizophrenia or severe depression; (6) pregnant or breastfeeding women; (7) fear of acupuncture and have a history of severe acupuncture adverse reactions; (8) participation in other studies related to LBP treatment within the past 3 months; and (9) cannot participate in regular treatment or observation, as required. Exclusion process will be conducted by the same researcher handling the inclusion.

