#### 2.3.4. Criteria for withdrawal, dropout, and removal

Participants presenting any of the following situations will be considered as the withdrawal cases: (1) the disease get worse after treatment in this study; (2) complications or severe adverse events (SAEs) occur during the trial; (3) the utilization of related treatments other than the study, which may impact upon the results of this study; (4) poor compliance, or the number of appointments for treatment does not meet the requirements (<80%); (5) unblinding for emergency situations; and (6) participants request to withdraw from the study.

Participants unable to complete the observation procedure of the study, regardless of the reasons, will be classified as dropout cases. The last outcome data of dropout cases will be included in data analysis. During the trial, participants will be removed if (1) they are wrongly enrolled due to misdiagnosis; (2) they do not accept the treatment after being enrolled in the study; (3) they participate in other clinical trials at the same time; and (4) the post-inclusion data is incomplete and there are no evaluable records for the analysis of the results. Data from withdrawal and dropout cases will be included in intention-to-treat analyses.

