#### 2.6.2. Control group

In the sham ACE group, the embedding needle and acupoints are the same as those of the intervention group, but no catgut will be placed into the needle tubing before being inserted into the acupoints, so that no catgut will be left under the tissue after the needle is pulled out. At the same time, the needle will be withdrawn immediately, because inserting to the acupoints at a depth of 1.0 cm without retaining the needle to activate the *qi*, which is essentially different from traditional acupuncture.

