#### 2.7.3. Safety assessment

Adverse events that happen during the study will be recorded in the CRFs in detail, including the time of occurrence, symptoms, duration, treatment methods, and outcomes. Adverse events will be assessed by the specialists in the panel, to determine whether the conditions are treatment related and whether further rescues are needed. Adverse events frequently occurring in ACE treatment include fainting, acupoint swelling, and subcutaneous hemorrhage, and will be addressed by symptomatic treatment methods. Once the adverse events are defined as severe, such as acupoints infection, allograft rejection, or major organ damage, the research process will be terminated and the inspectors of the monitoring panel will reveal the participant’s allocated intervention at once. Consequently, the participant will withdraw from the study and accept systemic treatments. The cost of treatments for adverse events arising from this study will be paid by the sponsor of this study. The monitoring panel will report the SAEs to the ethics committee, while the researchers will closely follow the participants’ condition, and record it in detail in the CRF.

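### Exclusion 7 joins needle fear and a past severe acupuncture reaction with 'and', so read literally a candidate with only one of them is not excluded

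*Protocol article*

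**What the plan says.** The list in section 2.3.3 opens with "Participants who meet any of the following conditions will be excluded", so one numbered item is enough to exclude. Item 7 reads "fear of acupuncture and have a history of severe acupuncture adverse reactions". Nothing else in the article restates or explains it.

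Other criteria that might bear on the same people are inclusion 4 in section 2.3.2 ("participate voluntarily in this study, signing written informed consent") and exclusion 9 ("cannot participate in regular treatment or observation, as required"). One researcher applies both the inclusion and the exclusion criteria.

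In the sham arm, section 2.6.2 states that "the embedding needle and acupoints are the same as those of the intervention group", without catgut. Section 2.6 has both arms treated every 2 weeks over 8 weeks. Section 2.7 makes the incidence of adverse events the safety outcome, and section 2.10 analyses it mainly descriptively.

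**The concern.** The opening *any* works between the numbered items. It does not reach inside item 7, where the *and* makes a joint condition. On that reading two kinds of candidate pass item 7: someone who reacted severely to earlier acupuncture but is not afraid of it, and someone who is afraid but has had no such reaction.

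The item appears to be there to keep such people from being needled. If it is applied as written, it does so only for those with both features. At stake is a foreseeable and avoidable exposure and, through it, the level of the adverse-event rates that the trial will report.

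**Working it through.** No figure in the plan depends on this wording, so the check is mainly textual.

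**1. Logic of the list.** Let F be fear of acupuncture and R a past severe reaction to it. Item 7 as written excludes F∩R. Two separate grounds would exclude F∪R. The rules differ for candidates with exactly one feature.

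**2. Wording of the neighbouring items.** Where another item names alternative grounds, it uses *or*. Item 5 is an example: "cognitive impairment or serious mental illnesses, such as schizophrenia or severe depression". Items 2, 4 and 6 do the same, item 3 uses *or* in its examples, and item 9 uses it between treatment and observation. Item 4 also contains *and*, but there it joins attributes of one type of disease. Item 7 is the only item that joins two distinct grounds for exclusion with *and*.

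**3. Whether another criterion closes the gap.**

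| Candidate | Item 7, read literally | Any other rule |
|---|---|---|
| F and R | excluded | not needed |
| F only | not excluded | none by rule; may decline consent (inclusion 4) or be judged unable to attend (exclusion 9) |
| R only | not excluded | none; the other items may catch a particular cause of the reaction, but not the history itself |

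**4. Exposure.** Section 2.6.1 uses two acupoints bilaterally, so 2 × 2 = 4 insertions per session, and the sham arm has the same points and needle. An R-only candidate is needled in either arm.

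**5. Size.** The share of candidates on whom the two readings differ is P(F) + P(R) − 2·P(F∩R). The article gives none of these terms. The values below are assumptions, and they show only how far the answer moves. Each share is applied to the planned 82 participants.

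- P(F) = 5%, P(R) = 2%, independent: 0.05 + 0.02 − 2 × 0.001 = 0.068, and 0.068 × 82 = 5.6. Of these, R only is 0.02 × 0.95 × 82 = 1.6.
- Same frequencies, every person with R also has F: 0.05 + 0.02 − 2 × 0.02 = 0.03, and 0.03 × 82 = 2.5, all of them F only.
- P(F) = 1%, P(R) = 0.5%, independent: 0.01 + 0.005 − 2 × 0.00005 = 0.0149, and 0.0149 × 82 = 1.2.

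These sums also treat volunteers as if they were all candidates. People who fear needling are the least likely to answer an advertisement and consent, which lowers the F-only share further. No one value can be defended from the document.

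**The case against.** The strongest reply is that the *and* is loose English for two separate grounds and that a clinician would read it so. The removal list in section 2.3.4 supports this. It closes with *and* and has no *any*, yet its four grounds can only sensibly be alternatives. The trial also has one centre and one screening researcher, and section 2.9 provides training in identifying eligible participants, so inconsistent screening is less likely than in a multicentre trial.

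This stands as an explanation of how the wording arose, and it means nobody should infer that such candidates are in fact being enrolled. The text permits it and no more. It does not remove the defect. In section 2.3.4 the *and* links numbered items, whereas in item 7 it sits inside one. If two grounds were meant, the sentence misstates the rule. With one person screening, a literal reading would run through the whole of recruitment.

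A reader might go further and infer that the safety comparison is distorted. The documents do not support that. Allocation is random and 1:1, so people with either feature are expected in equal proportion in both arms. The active procedure adds manipulation and catgut, so they might react more often in that arm, but that would be a real effect in the population enrolled, not bias.

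A reader might also infer a loss of primary-outcome data. Section 2.3.4 does make it a withdrawal ground that "complications or severe adverse events (SAEs) occur during the trial". However, section 2.7.3 says "Adverse events frequently occurring in ACE treatment include fainting, acupoint swelling, and subcutaneous hemorrhage" and has these treated symptomatically. Its examples of severe events are infection, rejection and organ damage, and nothing in the article ties fear or a past reaction to those. Data from withdrawn participants are kept in the intention-to-treat analyses, although later measurements could still be missed.

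**Conclusion.** The point holds as a drafting defect in an operative safety exclusion. Read as written, item 7 lets through a candidate with only one of its two features, and for a past severe reaction without fear no other criterion stops entry. The consequence is a permitted, avoidable exposure in either arm and a possible rise in the reported adverse-event incidence.

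The conclusion rests on the literal reading of one word and on the absence of any clarifying text. It needs no assumption about frequency. A figure such as 5 to 6 of 82 should not be quoted as the size of the problem: it needs assumed, independent frequencies and ignores self-selection. The point has no demonstrated effect on power, on the primary estimate or on the comparison between arms.

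**What to change.** Split item 7 into two numbered exclusions, one for fear of acupuncture and one for a past severe adverse reaction to it, or replace *and* with *or*. If the sponsor did intend a joint condition, the protocol should say so explicitly and give the reason.

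Tell the screening researcher how the item is to be read, because section 2.12 reports active enrolment and section 2.2 runs recruitment to December 2024. Record how the item has been applied so far.

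The change is one word or one extra line, taken through the modification and ethics approval route in section 2.1. The downside is that a few more screened candidates are excluded. The analysis does not change.

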### 2.5. Sample size

The VAS score is the primary outcome indicator for this trial. Based on the results of the pre-test, it is known that the VAS score in the control group was 4.64 ± 1.42 cm and is expected to be reduced by 1.02 cm after treatment with ACE, setting a two-sided test with α = 0.05, β = 0.10. A sample size of 34 cases per group was calculated using PASS 15 software. Considering the 20% lost to follow-up calculation, the final number of cases needed for at least two groups was 41, for a total of at least 82 participants included.

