### 2.6. Interventions

The ACE operation in this study will be carried out in accordance with the Acupuncture Technical Operation Standard of the People’s Republic of China for ACE. Participants in both groups will accept treatments once every 2 weeks, for an 8-week period. During treatment, participants will be separated in different treatment rooms to avoid communication. Both treatments will be conducted by trained acupuncturists who are qualified, have acupuncture affiliation, and experience in clinical practice for more than 3 years. During the treatment and observation period of the study, if the participant’s pain symptoms worsen, the oral NSAIDs drug celecoxib (Pfizer Pharmaceuticals Ltd.) (Frampton and Keating, 2007; Foster et al., 2018) will be given orally for 2 days at a dose of 200 mg twice daily. If pain remains unrelieved, participants will be withdrawn from the study.

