#### 2.6.1. Intervention group

(1)**Acupoints:** According to the theory of TCM and previous clinical practice experience, this study will select the bilateral acupoints of Shenshu (BL23) and Dachangshu (BL25). The position and depth of acupoints for needle insertion are in accordance with the Name and Location of Acupoints (GB/T12346-2006), a standard of The People’s Republic of China. Details of selected acupoints are shown in Table 1 and Figure 2.(2)**Preparation of ACE:** The main instruments utilized in the ACE treatment operation include an embedding needle, combinating of needle tubing and liner core, and absorbable surgical chromic catgut (Yangzhou Longhu Medical Instrument Co., Ltd., Yangzhou City, Jiangsu Province, China), all of which are disposable sterile products. The embedding needle is shown in Figure 3. Participants will stay in the prone position during the operation process.(3)**Operation procedures:** Firstly, the skin of the target acupoint region will be exposed and sterilized with iodophor. After disinfecting hands and wearing sterile gloves, the acupuncturists will cut the absorbable surgical chromic catguts into 1 cm long pieces, and place the small catgut into the pinpoint of the embedding needle tubing, where the liner core will be moved up 1 cm. Then, acupuncturist will use the thumb and index fingers to fix the acupoint, while, with the other hand, inserting the needle perpendicularly to the skin surface of the acupoint at a depth of approximately 1 cm. Secondly, acupuncturists will apply lifting, inserting, and twisting techniques to stimulate special sensations, presenting soreness, such as numbness, swelling, or radiation, but no pain, which are described as *Deqi* in TCM theory. Thirdly, by pressing down the liner core of the embedding needle, the catgut in the needle tubing will be embedded in the muscle layer. Finally, both the liner core and needle tubing will be pulled out of the acupoint, and the post-treatment acupoint will be covered by a cotton ball with tape for 24 h.

**TABLE 1 T1:** Locations of acupoints in the study.

	Acupoints	
	BL23 Bladder meridian	BL25 Bladder meridian
Needle insertion	On the lumbar region, on the same level of the second subspinous of the lumbar vertebra, and 1.5 cun lateral to the posterior midline.	On the lumbar region, on the same level of the fourth subspinous of the lumbar vertebra, and 1.5 cun lateral to the posterior midline.

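### The exclusion criteria do not bar a known catgut allergy, although the first ACE session leaves four pieces of chromic catgut in muscle

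*Protocol article*

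**What the plan says.** Section 2.3.3 of the protocol article sets out nine numbered exclusions and applies them to anyone who meets any one of them. The only item about past reactions is criterion 7: "fear of acupuncture and have a history of severe acupuncture adverse reactions". The Introduction says that ACE "is an innovative acupuncture method combined with traditional theory and modern materials", so a reaction to earlier ACE may count as a reaction to acupuncture.

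Section 2.6.1 describes the implant as absorbable chromic catgut of surgical grade, cut to 1 cm lengths. One length is left in the muscle at each of BL23 and BL25 on both sides. Section 2.6.2 states that the sham needle carries no catgut. On allocation, Section 2.1 says: "Participants will be divided randomly at a ratio of 1:1 into the ACE group or the sham ACE group".

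Two safeguards are stated for harm during the trial. Section 2.3.4 withdraws a participant if "complications or severe adverse events (SAEs) occur during the trial". Section 2.7.3 unblinds and withdraws a participant after a severe event, and names allograft rejection among its examples. Section 2.6 adds that the ACE operation "will be carried out in accordance with the Acupuncture Technical Operation Standard"; that standard is an outside document and is not reproduced.

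**The concern.** The active treatment is an implant, and the implant is the only material that the ACE group receives and the sham group does not. A patient already known to react to that material is the clearest person to keep out of the trial, and the list has no line for this patient. The protocol does foresee that tissue may respond badly to the implant: allograft rejection is given as a severe event, and criterion 4 excludes people whose skin and subcutaneous tissue absorb or repair poorly. A known hypersensitivity is a different condition from poor absorption, and it is not listed.

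What is at stake is the safety of an individual participant. Nothing here bears on the analysis, the power or the estimate.

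**Working it through.** The plan states no figure on this point, so the check is a reading of every place where such a patient could be stopped, followed by a count of the exposure.

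**1. Where could a known catgut reactor be stopped before the first implant?**

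| Place in the protocol article | What it covers | Reaches a known catgut allergy? |
|---|---|---|
| 2.3.1 Diagnostic criteria (4 items) | Site and duration of pain, leg-raising test, imaging | No |
| 2.3.2 Inclusion criteria (4 items) | Age, ongoing pain, VAS range, consent | No |
| 2.3.3, criterion 2 | Spinal disease, lumbar skin disease, bleeding disorder | No |
| 2.3.3, criterion 4 | Diabetes, impaired tissue absorption or repair | No; this is not an allergic reaction |
| 2.3.3, criterion 7 | Fear of acupuncture, past severe acupuncture reactions | Only if the reaction followed acupuncture or, on a wide reading, ACE |
| 2.3.3, criterion 9 | Inability to take part in treatment or observation | Not on its natural reading, which is attendance |
| 2.3.3, criteria 1, 3, 5, 6, 8 | Cauda equina syndrome, serious organ disease, cognitive or mental illness, pregnancy or breastfeeding, other studies | No |
| 2.6.1, five operator duties | Sterility, avoiding fat, full embedding, angle and depth, aftercare advice | No allergy check among them |
| Table 2, screening | Previous medical history is taken | The question could be asked here, but no criterion tells the researcher to act on the answer |

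**2. How far does criterion 7 reach?** On its widest reading it catches a severe reaction to earlier ACE. A reaction to a catgut suture in surgery is not an acupuncture reaction on any reading. Read literally, the word joining its two parts also requires both fear and a past reaction, so a patient with a past severe reaction but no fear would pass. That is a wording slip and a secondary point.

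**3. When do the stated safeguards act?** The withdrawal rule in 2.3.4 and the unblinding rule in 2.7.3 both respond to an event. For a reaction to the implant, the event can only follow the first implantation, which Table 2 marks on the day of allocation.

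**4. Exposure before those rules can act.**
- Acupoints (2.6.1): 2, each on 2 sides, with 1 piece per site.
- Pieces in the first session = 2 x 2 x 1 = 4.
- Length = 4 x 1 cm = 4 cm.
- Chance that an enrolled known reactor is allocated to ACE under 1:1 = 1/(1 + 1) = 1/2.

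The number of such patients cannot be calculated, because the documents give no rate of catgut hypersensitivity.

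**The case against.** **The operation standard may require a check.** The standard cited in Section 2.6 is not shown, and the five duties in 2.6.1 are not said to be all of it. If it requires the operator to ask about catgut before inserting the needle, implantation would be prevented even though the patient had already been allocated. This stands as a limit on the point: it cannot be said that no check exists, only that none is printed. A check at that stage would still come later than it should, since the patient would already be randomized.

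**The article may be condensed.** It may be, but the exclusion list is numbered, is worded as complete, and includes lesser matters such as recent participation in other studies. A list followed as printed lets this patient in. If the full protocol already has the criterion, the sponsor can say so at once.

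**Criterion 9 might serve.** One could argue that a person who cannot tolerate catgut cannot take the treatment as required. The sense of the clause is attendance, and a safety exclusion should not depend on stretching it.

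**A reader might infer repeated implantation.** Section 2.6 says "Participants in both groups will accept treatments once every 2 weeks, for an 8-week period", which gives 8/2 = 4 sessions and 4 x 4 = 16 pieces per participant. The five treatment visits marked in Table 2 give 5 x 4 = 20. For an arm of 41 these become 41 x 16 = 656 or 41 x 20 = 820 pieces. These totals do not measure the risk. A recognised reaction leads to withdrawal, and the two weeks between sessions allow time for it to be seen. Nearly all of the arm-wide pieces would go to people with no known sensitivity. The exposure that the documents support is the first four pieces.

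**The importance is not shown by the documents.** They nowhere discuss catgut allergy, and naming allograft rejection shows only that some tissue response is foreseen. This is fair, and it is why the point is rated as small.

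**Conclusion.** The point holds as a small patient-safety gap. The nine printed exclusions do not bar a known catgut allergy or hypersensitivity, and criterion 7 leaves out any reaction learned of outside acupuncture. The size is four 1 cm pieces in muscle before a stated withdrawal rule can respond, with a 1-in-2 chance of that for any known reactor who is enrolled.

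This rests on two assumptions: that the printed list is the list in use, and that the unseen operation standard is not relied on to close the gap.

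A reader might go further and infer that the trial's result is at risk, or that a material number of participants will be harmed. The documents support neither. They give no rate, and nothing in the omission alters the comparison between the groups. The wording of criterion 7 deserves correcting but adds no weight to the main point.

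**What to change.** 1. Add an exclusion to Section 2.3.3: *known allergy or hypersensitivity to catgut (including chromic catgut suture)*.
2. Check it within the previous medical history that Table 2 already places at screening. No new visit or test is needed.
3. Section 2.12 says that enrolment is under way, so put the same question to participants already enrolled before their next session. Ask both groups, so that the question does not reveal the allocation.
4. As a wording correction, change criterion 7 to *fear of acupuncture, or a history of severe adverse reactions to acupuncture*.

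The cost is one protocol amendment, approved by the project management group and the ethics committee as Section 2.1 provides, and the loss of any otherwise eligible patient with a known catgut reaction. The documents do not allow that number to be estimated.
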